#### Metabolism

Plasma samples will be collected using BD Vacutainer® CPT™ Mononuclear Cell Preparation Tube Sodium Citrate (BD Bioscience, USA) in accordance with the manufacturer’s instructions. Metabolites will be extracted from plasma using Bligh and Dyer’s method with some modifications [47]. Hydrophilic metabolite analysis will be performed using LC with a Discovery HS F5 column coupled with an LCMS-8060NX triple quadrupole mass spectrometer (Shimadzu, Kyoto, Japan) in multiple reaction monitoring (MRM) mode (LC/MS/MS in MRM mode) as described previously [48]. The analytical platform for hydrophilic metabolite analysis will be controlled using LabSolutions (version 5.80; Shimadzu, Kyoto, Japan). The quantitative content of the hydrophilic metabolites will be calculated using the peak area relative to the internal standard (IS). The obtained datasets will be analyzed using the KEGG database [49], pipelines for identifying differentially expressed metabolites, and weighted gene coexpression network analysis. Examples of data representation have been described in our previous publications [43, 46, 50].

#### Gut microbiota

Stool samples will be collected by each participant at home using a stool collection kit containing a preservation solution one week prior to one day before the collection of blood and cognitive function data; we will receive the stool samples from participants on the day of the data collection. According to the manufacturer and a previous validation study of the preservative solution, fecal microbiota profiles can be stably maintained at room temperature for approximately one month [51]. After the stool samples are received from the participants, these samples will be refrigerated at ≤ 4 °C until shipment to the analytical laboratory (TechnoSuruga Laboratory Co., Ltd., Shizuoka, Japan). The stool samples preserved with the kit will be sent to the analysis institution within 4 weeks of collection to conduct 16S rRNA analysis and measure short-chain fatty acids (SCFAs). To determine the bacterial composition of the stool samples, 16S rRNA amplicon sequencing will be performed [52, 53]. This method provides an overview of the community composition of a bacterial community and reveals differences between groups and changes within groups. In the analysis, DNA will be isolated from stored stool samples and amplified by PCR, and sequence reads will be determined using the Illumina MiSeq system. The sequence reads will be imported into Quantitative Insights into Microbial Ecology version 2 (QIIME2) and then analyzed for bacterial identification and diversity [54, 55]. The principal gut microbiota outcomes in this study will be alpha diversity and beta diversity. Alpha diversity will be assessed using indices such as the Shannon index and observed features, whereas beta diversity will be evaluated using distance metrics such as Bray–Curtis dissimilarity and UniFrac distances. In addition, SCFAs in stool samples will be measured by high-performance liquid chromatography using a post-column reaction with a detector, two tandem columns, and a guard column.

#### Cognitive function

We will use neuropsychological tests to evaluate the overall domains of executive function, working memory, inhibitory control, and cognitive flexibility [56]. The stop signal task of the Cambridge Neuropsychological Test Automated Battery (CANTAB) (Cambridge Cognition, Cambridge Ltd, UK) will be used to evaluate response inhibition. In this task, participants are required to respond to an arrow stimulus by selecting one of two options, depending on the direction in which the arrow points. If an audio signal (a beep) is presented with an arrow stimulus, participants must withhold making that response and not select an option. The spatial span task of the CANTAB is used to evaluate visuospatial working memory. In the test, white squares are shown on the screen, some of which briefly change color in variable sequence; then, the participant is required to select the boxes that changed color in the same order that they were displayed on the screen (for the forward test) or in the reverse order (for the backward test). The number of boxes in the sequence increases from two to nine. Cognitive flexibility will be assessed with the Wisconsin Card Sorting Test (WCST) [57, 58]. In the test, participants are required to sort a series of cards according to different rules and alter their strategy when the rules change unexpectedly. In this study, we will use the computerized version of the WCST: Computer version 4 (PAR. Inc., Florida, US).

#### Sleep

We will assess nighttime sleep quality using a self-rated questionnaire, the Pittsburgh Sleep Quality Index (PSQI), and the Epworth Sleepiness Scale (ESS) [59–62]. The PSQI can assess sleep quality and disturbance with items that evaluate various aspects of sleep, and the ESS can measure the severity of daytime sleepiness. We will use the total scores as outcomes for each sleep measurement.

#### Constipation

We will assess the condition of constipation with the constipation assessment scale [63]. This scale is a self-report questionnaire consisting of 8 items. The total score represents the severity of constipation.

#### Obesity

We will calculate body mass index (BMI) (kg/m^2^) to evaluate obesity.

#### Mental health

The Profile of Mood States 2nd edition (POMS 2) will be used to evaluate a wide range of mood states [64, 65]. We will use the total mood disturbance score and 7 subscales (e.g., depression and tension–anxiety) as indicators of mental health status.

#### Physical and psychological symptoms

We will use the Anti-aging Quality of Life Common Questionnaire (AAQOL) to evaluate participants' health status, including physiological and psychological symptoms [66]. We will use the total score and subtotal scores for physical and psychological symptoms as indicators of an individual’s health status.

#### Health-related quality of life

We will use the self-reported MOS 36-item short-form health survey version 2 (SF-36v2) to evaluate health-related quality of life (HRQOL) [67, 68]. The physical and mental component summary scores will be used as indicators of HRQOL.

#### Daily health checks

We will ask participants to report their health status and body temperature on a daily check sheet. Specifically, participants will be asked to report the presence or absence of the following symptoms: sore throat, running nose, cough, phlegm, stomachache, diarrhea, loss of appetite, and lethargy/fatigue.

#### Habitual diet

We will administer the BDHQ both before and after the intervention, allowing us to assess baseline dietary intake as well as changes during the intervention period, including the intake of brown rice and mixed grains [31]. If there are significant between-group differences in the habitual intake of whole grains (including brown rice) at baseline between intervention groups or if significant changes in the habitual diet are observed during the intervention, these variables will be included as covariates in the statistical analyses.

All copyrighted questionnaires and tests to be used in this study will be obtained and administered in accordance with the relevant licensing and permission requirements.

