### Outcomes {12}

Previous studies have suggested that brown rice has various effects on human health, and we will present evidence concerning these effects and the underlying mechanisms by using a brown rice-derived supplement in this study. Therefore, the overall condition of the immune system, metabolism, constipation, sleep, cognitive function, mental health, and gut microbiota community composition will be co-primary outcomes for comprehensively examining various health aspects. Blood samples will be collected to analyze immune function and metabolism via transcriptome and metabolome analysis, respectively, and stool samples will be collected to evaluate diversity in the gut microbiota.

In addition, we will collect information on the factors that may influence the relationships between consumption of the brown rice-derived supplement and primary outcomes. Various lifestyles could influence the relationships between the consumption of the brown rice-derived supplement and broad health conditions. In particular, daily eating habits and physical activity may strongly impact these relationships. Therefore, we use the brief-type self-administered diet history questionnaire (BDHQ) and a simple questionnaire to evaluate total and domain-specific physical activity [31, 32]. In addition, we will collect data on the overall intelligence quotient (IQ) to control for the influence of IQ on the performance of cognitive tests [33].

Since this study aims to determine the effects of brown rice-derived supplement consumption on various health aspects, all sample collection and measurements, except for daily health, will be performed at two time points (baseline and endpoint), and we will compare the changes in these variables between and within groups. Daily health during the intervention period will be compared between groups. We assume that these variables will change in a positive direction if the brown rice-derived supplement is effective at improving human health.

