## Statistical methods

### Statistical methods for primary and secondary outcomes {20a}

The co-primary outcomes will be analyzed to determine whether the consumption of the brown rice-derived supplement is superior to the use of a placebo in terms of positive health effects. The data derived from transcriptome and metabolome analysis will be compared between intervention groups after relevant covariates are controlled for. Microbiome and overall community composition will be compared between intervention groups on the basis of alpha and beta diversity with relevant covariates controlled for. For cognitive function, all outcomes will be compared through an analysis of covariance, with the intervention group set as a between-group factor, the data collection time points as a within-group factor, and the covariates as relevant covariates. The BMI and questionnaire data will be compared through an analysis of covariance controlling for relevant covariates. For continuous variables, the distribution of the data and the fulfillment of the model assumptions will first be assessed. Parametric methods will be used when the relevant assumptions are met; otherwise, appropriate nonparametric methods will be applied.

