### Methods for additional analyses (e.g., subgroup analyses) {20b}

Not applicable as, no additional analyses are planned in this study.

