### Methods in analysis to handle protocol non-adherence and any statistical methods to handle missing data {20c}

The primary analysis will be based on the intention-to-treat (ITT) principle, but we will include only the randomized participants who participate in data collection at both the baseline and the study endpoint, irrespective of their degree of adherence to experimental food consumption. In this study, we will exclude randomized participants who drop out of the study and do not provide endpoint data, as this study aims to examine the effect of the nutritional supplement on healthy adults, and we do not expect as great an effect as when medication is administered to a patient group. To follow the ITT principle as closely as possible, all the participants will be asked to participate at the endpoint as much as possible. A per-protocol analysis limited to participants with adherence ratios greater than 80% will be performed as a sensitivity analysis. Every effort will be made to prevent missing values during the data collection process, and we will address any missing data using multiple imputation or regression imputation.

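### Habitual diet enters the models only if a significance test fires, and one trigger is diet change measured after randomisation: the first costs power, the second can bias the effect estimate

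*Protocol article*

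**What the plan says.** The Habitual diet section of the protocol article sets two conditions for adjustment. The first is "significant between-group differences in the habitual intake of whole grains (including brown rice) at baseline". The second is a change in diet during the trial: "if significant changes in the habitual diet are observed during the intervention, these variables will be included as covariates in the statistical analyses". The final clause serves both conditions. No significance level is given, and the text does not say whether the change is tested between or within arms.

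Diet change is a post-randomisation variable by design: "We will administer the BDHQ both before and after the intervention". Outcomes {12} explains why diet is recorded: "daily eating habits and physical activity may strongly impact these relationships".

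The statistical methods section {20a} speaks only of relevant covariates, without listing them, for example "The BMI and questionnaire data will be compared through an analysis of covariance controlling for relevant covariates". Section {20c} describes the main analysis: "The primary analysis will be based on the intention-to-treat (ITT) principle". Section {20b} adds that "no additional analyses are planned in this study". The diet rule is therefore not set apart as a sensitivity or mediation analysis. As written, it governs the main models.

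**The concern.** The two triggers do different kinds of harm.

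**Baseline trigger.** In a randomised trial, a significant baseline difference is a chance event. The test does not ask what matters for a covariate, which is whether it predicts the outcome. Diet is singled out in advance as potentially important, yet it would enter the model only in the small fraction of trials where the test happens to fire. The precision it might bring is usually lost.

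**Change trigger.** Diet change occurs after allocation and may be a consequence of the product. If it is, adjusting for it does one or both of two things. It removes the part of the effect that runs through diet. It also opens a path through unmeasured factors that influence both diet and outcome. The adjusted estimate is then no longer the randomised comparison that the superiority aim in {20a} calls for. The trigger also fires most often when the product really does shift diet, which is when adjustment does harm.

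**Working it through.** **Inputs from the protocol article.** 40 analysed per arm (Sample size {14}); 1:1 allocation (Trial design {8}); diet questionnaire before and after the intervention (Habitual diet). The article gives no alpha, power, effect size or diet-outcome correlation, so it has no figure of its own to reproduce here.

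**Assumptions.** Two-sided 5% tests, outcome SD 1, linear model with treatment, and correlations and diet shifts varied as shown. Results come from simulation; separate runs agree to about one percentage point of power.

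**1. Baseline trigger.** Model: outcome = effect × arm + r × baseline diet + noise, with total SD 1. Baseline diet is independent of arm, so a 5% test fires in about 5% of trials and the covariate is omitted in about 95%. Power for a true effect of 0.5 SD:

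| Diet-outcome correlation r | Under the stated rule | Always adjusted |
|---|---|---|
| 0.1 | about 61% | about 61% |
| 0.3 | about 59% | about 63% |
| 0.5 | about 61% | about 71-72% |
| 0.6 | about 60-61% | about 78-79% |

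The estimate is unbiased in every row. Type I error under the rule is at or a little below 5%: 4.8% at r = 0.3, 4.3-4.4% at 0.5 and 4.0% at 0.6.

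**2. Change trigger, shared cause, no true effect.** An unmeasured factor correlates c with both diet change and outcome, and the product shifts diet by a (in SD).

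- If diet change were always in the model, the bias would have size c² × a. For a = 0.5 this is 0.25 × 0.5 = 0.125 at c = 0.5, and 0.36 × 0.5 = 0.18 at c = 0.6.
- The rule adjusts only when the test fires. For a = 0.5 a between-arm test fires in about 59% of trials. Averaged over all trials, the bias is about 0.10 SD (type I error about 7%) at c = 0.5, and about 0.14 SD (9-10%) at c = 0.6.
- For a = 0.2 the bias is about 0.02 SD and type I error stays at about 5%.
- For a = 0 there is no bias.

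A within-arm trigger gives a similar picture: about 0.07 SD at a = 0.5, c = 0.5. The sign of the bias depends on the signs of the correlations.

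**3. Change trigger, diet as mediator.** The product shifts diet by 0.5 SD, diet affects outcome by 0.3 per SD, and the direct effect is 0.35. The total effect is 0.35 + 0.5 × 0.3 = 0.50 SD.

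- Without adjustment for diet change: estimate 0.50, power about 56%.
- Always adjusted: estimate 0.50 - 0.15 = 0.35.
- Under the rule: about 0.39 with a between-arm trigger (power about 37%), or about 0.41 with a within-arm trigger (power about 42%).

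**The case against.** **The product may hardly change diet.** It is one 3.5 g stick a day (15.16 kcal against 13.27 kcal for placebo), given blinded, to people asked not to alter their eating deliberately. No passage supports a shift as large as 0.5 SD. This stands: the bias is conditional, and small for small shifts. But the request covers only intentional change, and the trial itself studies constipation, mood, BMI and appetite symptoms, so an effect on eating is not far-fetched. The rule stays in force either way.

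**Baseline diet may predict little.** Habitual brown rice consumers are excluded, which may narrow the variation. What counts is the correlation left after the outcome's own baseline is allowed for. This also stands: at a correlation of 0.3 or below the loss is about 4 points or less.

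**The covariate list may sit in an analysis plan that is not shown.** True, and its absence is no fault. The point concerns a rule that the article does state. The unlisted covariates could include baseline diet unconditionally, but no text says so.

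**Stronger readings that the documents do not support.**

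- A reader might infer a false effect of 0.12-0.18 SD with type I error of 8-12%, or the loss of the entire mediated 0.15 SD. Those figures describe unconditional adjustment, and the plan's rule is conditional.
- A reader might infer that the baseline trigger biases the estimate or inflates type I error. It does neither.
- A reader might take Outcomes {12} as saying that diet strongly affects the outcomes. It says only that diet may do so, and refers to the supplement-health relationships, so diet is not established there as prognostic.

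**Conclusion.** The point holds in two separate parts and should be fixed.

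The baseline trigger is an efficiency fault. It forfeits nearly all the precision that baseline diet could bring: from nothing at a correlation of 0.1, through about 4 points of power at 0.3 and 10 at 0.5, to nearly 20 at 0.6. This assumes a 0.5 SD effect and 40 per arm.

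The change trigger is a potential validity fault, because it lets a possible consequence of treatment into the primary models. Its size rests on an assumed effect of the product on diet. With a 0.5 SD shift it is material, both as a false effect and as attenuation of a mediated effect. With a 0.2 SD shift it is negligible, and with no shift it is absent. The documents do not allow these cases to be told apart in advance. That argues for removing the rule, but it does not show that the trial's results will be biased.

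**What to change.** In the Habitual diet section, delete both significance triggers.

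- Name baseline whole-grain or fibre intake from the diet questionnaire as a pre-specified covariate, included whatever any baseline test shows.
- State that diet change during the intervention is not a covariate in the primary effect models. Report it by arm descriptively, or use it only in a labelled exploratory mediation or sensitivity analysis. Section {20b} would then need to mention that analysis.

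Settle this before the allocation is revealed for analysis. The data are already being collected, so the cost is wording and one degree of freedom per model. Which other baseline covariates to include is a separate choice that this point does not dictate.

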### Plans to promote participant retention and complete follow-up {18b}

We will try to improve adherence to the intervention by asking participants to report their consumption of the supplement on the application and by sending a reminder message to participants each day if they do not report consumption by 19:00. Furthermore, we will provide additional incentives to participants for retention in the study if the data collected for endpoint evaluation are complete.

### Data management {19}

Blood and stool samples will be preserved properly after preprocessing for analysis. All cognitive assessments will be conducted using digital software on tablets and laptops to avoid errors associated with data entry. All data collected using paper-and-pen methods will be entered into spreadsheets and double-checked. Paper forms will be stored securely in a locked cabinet that only study staff will be able to access. All the research staff who complete the data collection will be trained to avoid missing data and will be asked to record their data collection processes for reference and to manage any potential data collection issues. For quality control, all data, regardless of collection methods, will be reviewed to identify response patterns, response ranges, out-of-range codes, and internal inconsistencies.

### Confidentiality {27}

All data and samples obtained in the trial will be stored securely at the study site in pseudonymized form, thus preventing participants from being identified without the corresponding table. The corresponding table will be stored electronically, and access will be limited to study staff members who handle inclusion and clinical data acquisition. All documents containing personal information, such as the informed consent form, will be stored separately from the study records. The data and samples will be archived for at least five years after the end of the study.

### Plans for collection, laboratory evaluation and storage of biological specimens for genetic or molecular analysis in this trial/future use {33}

Blood samples will be collected from 9:0012:00 after a 13-h fasting period. After collection, the blood samples will be divided to obtain PBMCs, and the plasma will be stored in a microtube at − 80 °C. For analyses of immune function and metabolism, total RNA will be extracted from PBMCs, after which RNA-seq libraries will be generated using the NEBNext Globin & rRNA Depletion Kit and the NEBNext UltraII Directional RNA Library Prep Kit. Sequencing experiments will be performed with the NextSeq 500 system. Data analysis will be performed as described in the “ Immune function” section.

Metabolites from plasma will be extracted using Bligh and Dyer’s method with some modifications. Hydrophilic metabolites will be analyzed will be performed using LC with a Discovery HS F5 column coupled with an LCMS-8060NX triple quadrupole mass spectrometer (Shimadzu, Kyoto, Japan) in MRM mode. Data analysis will be performed as described in the “ Metabolism” section.

At each visit, a stool sample will be collected with a kit containing a preservation solution and sent to the laboratory (TechnoSuruga Laboratory Co., Ltd., Shizuoka, Japan) to analyze the gut microbiota and SCFAs. The samples will be preprocessed for analysis immediately after arrival at the laboratory. Furthermore, microbial genomic DNA will be extracted from the stool samples, and template DNA will be subjected to 16S RNA gene amplicon sequencing using Illumina MiSeq.

## Statistical methods

### Statistical methods for primary and secondary outcomes {20a}

The co-primary outcomes will be analyzed to determine whether the consumption of the brown rice-derived supplement is superior to the use of a placebo in terms of positive health effects. The data derived from transcriptome and metabolome analysis will be compared between intervention groups after relevant covariates are controlled for. Microbiome and overall community composition will be compared between intervention groups on the basis of alpha and beta diversity with relevant covariates controlled for. For cognitive function, all outcomes will be compared through an analysis of covariance, with the intervention group set as a between-group factor, the data collection time points as a within-group factor, and the covariates as relevant covariates. The BMI and questionnaire data will be compared through an analysis of covariance controlling for relevant covariates. For continuous variables, the distribution of the data and the fulfillment of the model assumptions will first be assessed. Parametric methods will be used when the relevant assumptions are met; otherwise, appropriate nonparametric methods will be applied.

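### The cognition model treats baseline as an outcome; adjusting the endpoint for baseline is at least as precise when variances are equal, and the planned within-group comparison should be labelled descriptive

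*Protocol article*

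**What the plan says.** Outcomes {12} makes cognition co-primary: "cognitive function, mental health, and gut microbiota community composition will be co-primary outcomes". Apart from daily health, all measurements "will be performed at two time points (baseline and endpoint), and we will compare the changes in these variables between and within groups".

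Statistical methods {20a} states the aim of the co-primary analyses as showing that the supplement is "superior to the use of a placebo in terms of positive health effects". For cognition the model given there is: "analysis of covariance, with the intervention group set as a between-group factor, the data collection time points as a within-group factor". Adjustment is mentioned only in general terms, and the baseline score of the test is not named as a covariate. Outcomes {12} does say that IQ is collected so that its influence on cognitive performance can be controlled.

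The other measures are handled differently: "The BMI and questionnaire data will be compared through an analysis of covariance controlling for relevant covariates". That sentence has no time factor.

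**The concern.** With one baseline and one endpoint, making time a within-group factor puts the pre-randomisation score on the outcome side of the model. Treatment cannot have affected that score. It is more useful as a covariate, where it removes between-person variation from the endpoint comparison. Subtracting it in full, as a change score does, is optimal only when baseline and endpoint are almost perfectly correlated.

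The precision is worth having. The section on non-adherence and missing data {20c} says that effects as large as those of medication in patients are not expected. The section also restricts the primary analysis to participants with data at both time points.

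The second part concerns wording. A change within one arm mixes any supplement effect with whatever moves both arms between two administrations of the same test. If within-arm changes carry p-values, a result that is significant under the supplement and not under placebo could be taken for benefit when the arms do not differ.

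**Working it through.** **Inputs from the Protocol article.** 40 per group, 96 recruited, 20% dropout (Sample size {14}); 1:1 allocation (Trial design {8}); two time points (Outcomes {12}); analysis of participants with both (section {20c}).

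**Assumed, because not given.** Two-sided alpha 0.05, effect 0.5 SD (and 0.2 SD for comparison), rho from 0.3 to 0.9, equal SD at both time points.

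**The plan's own figure.** The 40 per group is taken by reference to an earlier trial, with no effect size, SD, alpha or power, so it cannot be recomputed. Expected completers: 96 × 0.8 = 76.8, or about 38 per arm.

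**Variances (SD at each time point = 1).**
- Group by time with two time points and complete pairs is a t-test on change. Variance per person: 2(1 − rho).
- ANCOVA of the endpoint on baseline. Residual variance per person: 1 − rho² = (1 − rho)(1 + rho).
- Ratio, ANCOVA to change: (1 + rho)/2.

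**Example, rho 0.5.** Change: SD = √1.00 = 1.00, SE = 1.00 × √(2/38) = 0.229, effect/SE = 0.5/0.229 = 2.18, power 58%. ANCOVA: SD = √0.75 = 0.866, SE = 0.199, effect/SE = 2.52, power 70%.

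**Power with 38 per arm (t distribution).**

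| rho | Variance ratio | 0.5 SD: change → ANCOVA | 0.2 SD: change → ANCOVA |
|---|---|---|---|
| 0.3 | 0.65 | 44% → 62% | 11.2% → 14.7% |
| 0.5 | 0.75 | 58% → 70% | 13.8% → 16.9% |
| 0.7 | 0.85 | 79% → 85% | 19.9% → 22.6% |
| 0.8 | 0.90 | 92.5% → 94.8% | 27.5% → 30.0% |
| 0.9 | 0.95 | 99.8% → 99.9% | 48.6% → 50.6% |

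A simulation with 40 per arm (20,000 trials per setting, 0.5 SD) gave 60.1% against 72.2% at rho 0.5 and 81.4% against 86.8% at rho 0.7. Type I error was about 5% for both methods.

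**Within-arm tests when the arms do not differ.** Suppose both arms share the same drift, expressed in SDs of change, and each is tested with a paired t-test on 38 people. If p is the chance that one arm is significant, exactly one of two independent arms is significant with probability 2p(1 − p).

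| Shared drift | p | Exactly one arm significant |
|---|---|---|
| 0 | 0.050 | 2 × 0.050 × 0.950 = 9.5% |
| 0.1 | 0.092 | 17% |
| 0.2 | 0.225 | 35% |
| 0.3 | 0.437 | 2 × 0.437 × 0.563 = 49% |
| 0.5 | 0.851 | 25% |
| 0.6 | 0.950 | 10% |

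In half of these cases the significant arm is the supplement arm. The expression cannot exceed 50%, so a drift of 0.3 is close to the worst case.

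**The case against.** The planned cognition analysis is valid. Under 1:1 randomisation the group-by-time test is unbiased and holds its type I error, so a reader who infers a biased or wrong test goes further than the documents allow. This objection stands: the point concerns efficiency and naming the contrast.

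Four stronger readings are tempting and do not hold.

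- **That positive change counts as efficacy.** The sentence "We assume that these variables will change in a positive direction if the brown rice-derived supplement is effective at improving human health" runs from efficacy to change. It states the direction of the hypothesis and is not a decision rule. Objectives {7} and Statistical methods {20a} both set the comparison against placebo.
- **That within-arm significance tests are planned.** Outcomes {12} says only "we will compare the changes in these variables between and within groups". It names no test or p-value, and Statistical methods {20a} lists no within-arm test. The comparison may be descriptive already; the text does not say.
- **That the group main effect, which would average baseline with endpoint and halve the effect, is the test.** No section says so, and comparing changes between groups points to the interaction.
- **That the same fault affects BMI, the questionnaires and alpha diversity.** These are to be adjusted for relevant covariates, which may include the baseline value. A condensed article can leave that list to the full plan.

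The phrase on covariates might also be read as putting the baseline score into the cognition model. That is a weak defence, because the score is already an outcome there.

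The size is conditional too. The documents give neither rho nor an effect size, and the gain is small when rho is high or the effect is small. Retest gain on the cognitive tests is likewise an assumption.

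**Conclusion.** The point holds for cognition as a worthwhile improvement, not as an error that invalidates the analysis. With equal variances at the two time points, the baseline-adjusted estimate has 65% to 95% of the variance of the change-score estimate for rho 0.3 to 0.9. At an assumed 0.5 SD the gain in power is about 17 points at rho 0.3 (44.4% to 61.6%), 12 at 0.5, 6 at 0.7, 2 at 0.8 and almost nothing at 0.9. At 0.2 SD it is about 2 to 4 points throughout.

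The within-group wording is a lesser matter. With no true difference, and an assumed shared drift of 0 to 0.3 SD of change, one arm alone would be significant in about 10% to 49% of trials if both were tested. That shows why such results cannot support superiority over placebo. It does not show that the investigators intend to use them that way.

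**What to change.** In Statistical methods {20a}, for each cognitive outcome, specify: endpoint score = arm + baseline score of the same test + prespecified baseline covariates such as IQ. Name the adjusted between-arm difference at the endpoint, with its 95% CI, as the inferential result. If a repeated-measures model is preferred, constrain the baseline means to be equal across arms and name the endpoint contrast as the test.

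In Outcomes {12}, state that within-group changes are descriptive (mean and SD, without p-values) and that inference rests on the between-group comparison.

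The cost is a wording amendment. Baseline scores and IQ are already collected, and no visit, measurement or participant is added.
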